#### RCT secondary outcome measures

In addition, data will be collected on the following items:

1. Costs are assessed from a societal perspective. Units of direct health care utilisation, both within and outside the health care sector, as well as productivity loss due to absenteeism and presenteeism are collected by cost diaries. Examples of direct health care units within the health care sector include consultations with the general practitioner, hospitalisations, and medications, and examples of direct health care units outside the health care sector include over-the-counter medication, informal care, and consultations with alternative health professionals. Costs will be calculated by multiplying the volume of resource use by cost prices, following the Dutch guidelines for economic evaluations in health care to estimate costs [15].

2. Health is measured with the RAND-36, a Dutch translation of the 36-Item Short Form Health Survey (SF-36) [16,17] and the EuroQol. The RAND-36 is a set of generic, coherent, and easily administered quality-of-life measures. It taps eight health concepts: physical functioning, bodily pain, role limitations due to physical health problems, role limitations due to personal or emotional problems, emotional well-being, social functioning, energy/fatigue and general health perceptions. It also includes a single item that provides an indication of perceived change in health. The Dutch version has a good reliability, good validity and is sensitive for changes [18]. Moreover, quality of life is also assessed with the EQ-5D also known as EuroQol (T2-T5) [19].

3. Satisfaction with the intervention is measured with the question, "Are you satisfied with the contact 6 weeks after delivery?", which can be answered on a six-point Likert scale. This question will be asked at 12 weeks after delivery.

4. Self-reported feelings of recovery from complaints, also called global perceived effect (GPE) is measured with the question, "To what extent have your complaints changed since 6 weeks after the delivery?", which can be answered on a seven-point Likert scale, with a range from "1" (completely recovered) to "7" (worse than ever). Again, this question will be asked at 12 weeks after delivery.

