### Blinding

Given the nature of the intervention, only the control group supervisors and participants are blinded to the intervention. The intervention group supervisors and participants cannot be blinded for the allocated treatment. Furthermore, the researcher and research assistant cannot be blinded for the allocated treatment. However, the data entry assistants are blinded for the allocated treatment. Data on sick leave and RTW are extracted from the routine databases of the company or the OHSP, thus, blinding does not play a role. The data will be blinded for the performance of the analysis. To guarantee blinding of the data for the analysis the participants, supervisors and companies are coded.

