### Outcome assessment

All measurements, except sick leave data of OHSP or company, are performed by questionnaires. The baseline measurement consists of two parts: The first part (T0) when the employee makes herself known as participant; and the second part at 30 weeks pregnancy (T1). There is a one-year follow-up with assessments at six weeks (T2), 12 weeks (T3), 24 weeks (T4) and 52 weeks (T5) after the delivery date.

Units of health care use and productivity loss which are used to calculate costs are measured at six weeks (except work performance), 12 weeks (except work performance), 18 weeks, 24 weeks and 52 weeks after the delivery date. If a woman takes sick leave, has health care costs or has decreased work performance at 24 weeks, she receives a questionnaire on units of health care use and productivity loss again at 30 weeks, and if indicated by the same criteria also at 36, 42 and 48 weeks after the delivery date. Self-reported sick leave is assessed as part of the cost measurements, and objective sick leave data is obtained from the databases of the OHSP and, if available, from the databases of the company.

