### Analysis

For the RCT, data will be analysed using statistical tests such as linear regression analysis and Cox regression analysis. The dependency of the observations will be taken into account by performing a multilevel analysis. The multilevel analysis will be performed with a four-level data structure where time, participants, supervisors and companies will be defined as levels 1, 2, 3 and 4, respectively. The analyses will be adjusted for baseline and prognostic dissimilarities, if necessary. Both an intention-to-treat analysis and a per-protocol analysis will be performed. For the cohort study, multilevel analysis will be performed with a three-level data structure where time will be defined as level 1; participants, level 2; and the companies, level 3.

The economic evaluation, which will be performed from a societal perspective, will consist of an analysis of differences in the total, direct and productivity loss costs between the intervention and control group, as well as a cost-effectiveness and cost-utility analysis of the intervention compared to common practice. In the cost-effectiveness analysis, sick leave will be the effect measure and the total costs will comprise all costs except those of productivity loss. Utilities will be based on the Euroqol questionnaire [19]. Quality Adjusted Life Years (QALY) will be calculated by multiplying the utility with the amount of time a patient spends in this particular health state. Incremental costs per QALY gained will be calculated applying both Dutch and UK tariffs. Bootstrapping methods will be used to estimate 95% confidence intervals for the incremental cost-effectiveness ratios and to derive cost-effectiveness planes and acceptability curves.

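### Absenteeism is costed from women's self-report although database sick-leave records are obtained for the same women; the records should be the main source, with self-report as fallback and sensitivity analysis

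*Protocol article*

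**What the plan says.** In the protocol article, item 1 of RCT secondary outcome measures sets a societal perspective and says that "productivity loss due to absenteeism and presenteeism are collected by cost diaries". Outcome assessment names two sources of absence data: "Self-reported sick leave is assessed as part of the cost measurements, and objective sick leave data is obtained from the databases of the OHSP", with company databases added where they are available. So self-report belongs to the costing. The Blinding section relies on the other source for the trial's outcomes: "Data on sick leave and RTW are extracted from the routine databases of the company or the OHSP, thus, blinding does not play a role".

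On who knows the allocation, the same section says that "The intervention group supervisors and participants cannot be blinded for the allocated treatment" and that "only the control group supervisors and participants are blinded to the intervention".

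Outcome assessment schedules the cost forms at six weeks and then at "12 weeks (except work performance), 18 weeks, 24 weeks and 52 weeks after the delivery date". Beyond week 24 there is a condition: "If a woman takes sick leave, has health care costs or has decreased work performance at 24 weeks, she receives a questionnaire" at week 30, and again at 36, 42 and 48 weeks if the same criteria are met.

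The Analysis section plans between-group comparisons of total, direct and productivity-loss costs, a cost-effectiveness analysis and a cost-utility analysis. It says that "In the cost-effectiveness analysis, sick leave will be the effect measure", and the same sentence excludes productivity loss from the costs of that analysis. Utilities for the cost-utility analysis come from the EuroQol.

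**The concern.** Presenteeism can only be asked of the woman herself. Absence is different, because the trial already obtains data on it that the article itself calls objective. Total days of sick leave in the first year is one of the primary indicators, and reducing those days is the trial's hypothesis, so absenteeism is the productivity component that the intervention targets. Taking it from self-report raises three problems.

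- Reporting may differ by arm, because one arm knows its allocation and the other is said not to.
- The intensity of measurement after week 24 depends on sick leave, which the intervention is meant to change.
- The report could show one absence total as the primary result and another in the productivity costs of the same women, and the article does not say which source prevails.

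**Working it through.** There is no stated figure to reproduce. What can be checked is the spacing of the cost forms and where self-reported absence enters the economic analysis.

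**1. Spacing of forms** (weeks from Outcome assessment, counted from delivery)

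- Not flagged at week 24: forms at 6, 12, 18, 24 and 52. Successive gaps are 6, 6, 6, 6 and 52 − 24 = 28 weeks.
- Flagged every time: forms at 6, 12, 18, 24, 30, 36, 42, 48 and 52. All gaps are 6 weeks except the last, 52 − 48 = 4 weeks.
- Flagged at week 24 but later no longer meeting the criteria: the final gap is 52 − 30 = 22, 52 − 36 = 16 or 52 − 42 = 10 weeks, according to the last extra form.

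**2. The 28-week gap against the time at risk of sick leave**

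The Background section puts leave after delivery at 10–12 weeks.

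- Weeks from end of leave to week 52: 52 − 10 = 42, or 52 − 12 = 40.
- Share covered by the single form at week 52: 28/42 = 67%, or 28/40 = 70%.

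This is a share of calendar time among women not flagged at week 24. It is not a share of absence days or of cost. The article gives neither the size of that group nor its absence after week 24.

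**3. Dependence of the schedule on the outcome**

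Sick leave is one of the three criteria for the extra forms; the others are health care costs and decreased work performance. If the intervention reduces sick leave around week 24, fewer intervention women qualify through that criterion, and more may fall into the 28-week gap. Any error that grows with the length of the gap could then differ between arms, even if every woman reports in good faith.

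**4. Where self-reported absence enters the economic analysis**

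| Planned analysis | Contains absenteeism cost? |
|---|---|
| Difference in productivity-loss costs | Yes |
| Difference in total costs | Yes, from the societal perspective |
| Difference in direct costs | No |
| Cost-effectiveness, sick leave as effect | No; productivity loss is excluded |
| Cost-utility, QALYs as effect | Only if its costs include productivity loss, which the article does not state |

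**The case against.** The strongest reply is that this is one component of a secondary outcome, and that the records are not shown to be the better source. Much of that is fair.

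- **Completeness of the records is not established.** Company data come only where available, across 15 companies. The specific RCT criteria require employment only until six months after delivery, so a woman who changes employer after that may leave the database for part of weeks 24–52. This stands, and it is why self-report must remain as a fallback.
- **The records may not be free of the intervention's influence.** Intervention supervisors know the allocation, and the Intervention group section describes a faster OHSP sick-leave procedure for women who want support. This also stands, and is a reason to check completeness by arm. It does not favour self-report, because the article relies on these same records for the primary outcome.
- **Long recall is inferred.** The costs item speaks of diaries and Outcome assessment of questionnaires, and no recall period is given. A diary kept as events occur would lessen the recall problem, though it would still depend on being kept up and returned.
- **The extra forms go where problems are.** The adaptive schedule follows women with current difficulties more closely. That is sensible for capturing cost, but new absence after week 24 in the other women is still covered by one form.
- **An article may leave the choice of source to a fuller document.** That would answer a silence. Here the article states the source for costing, so the point concerns a stated choice.

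A reader might also infer that the cost-effectiveness ratio would set recorded sick days against differently counted sick days. The Analysis section rules that out, because productivity loss is not in the costs of that ratio.

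**Conclusion.** The concern holds as a poor choice of source for absenteeism costs. Self-report is exposed to differential reporting between an unblinded arm and an arm said to be blinded, and to a form schedule that depends on sick leave, leaving 28 weeks on one form for women not flagged at week 24. What is affected is the comparison of total and productivity-loss costs, any cost-utility costs that include productivity loss, and the agreement of these with the primary sick-leave result.

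Size and direction of bias cannot be derived from the document. A percentage for over- or under-reporting would only restate an assumption, so none is given. The 67–70% rests on leave ending 10–12 weeks after delivery and on the woman not being flagged at week 24.

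Three stronger readings are not supported: that reporting is unblinded in both arms, that the records are complete to week 52, and that a 28-week recall is prescribed.

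**What to change.** State in the economic analysis that:

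1. In the main analysis, absenteeism is valued from the OHSP and company records, from the end of maternity leave to week 52. Days are converted to hours with the working hours asked at T0 and T3 (Table 1), allowing for partial return.
2. Self-reported absence is used where records are missing or end early, for example after a change of employer beyond six months.
3. The analysis is repeated with self-report throughout as a sensitivity analysis.
4. Self-report remains the source for presenteeism and health care use.
5. Completeness of the records is reported by arm.

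No new measurement is needed, since the records and working hours are already collected. The cost is the added analysis text, the conversion of days to hours for part-time work and partial return, and the completeness check.

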#### Cohort study outcome measures

In the cohort study, data will be collected on whether certain complaints develop or if RTW occurs among the participants.

1. The first outcome measure for the cohort is the presence of complaints of pregnancy-related pelvic girdle pain (PPGP). Two aspects on PPGP are measured: pain intensity and functional status. Pain intensity is measured with the same method as used in the Maastricht PPGP cohort study [20]. It is a self-report measure and contains questions whether the woman experiences pain at the lower back, buttocks, the symphysis pubis, groin or radiation into either or both legs on a eleven-point scale where zero is defined as "no pain" and 10 as "much pain". Functional status is measured with the Roland-Morris Disability-24 questionnaire (RDQ-24) [21]. The RDQ-24 is widely used in low back pain and pregnancy-related pelvic girdle pain research, and is tested by Riddle[22]. A validated Dutch version of the RDQ-24 is used in the study[23]. Both the test-retest reliability and construct validity of this questionnaire are considered good [22]. For the purpose of this study, the formulation of the items in the RDQ-24 was modified to read for 'my pelvic pain and/or low back pain' instead of 'my back pain'.

2. The second outcome measure for the cohort is fatigue, measured in two ways. Firstly, self-reported fatigue is rated on an eleven-point scale anchored by "0" for "no complaints" and "ten" for "many complaints". Secondly, fatigue is measured with the Checklist Individual Strength (CIS) questionnaire [24]. The CIS is a Dutch self-report questionnaire containing 20 items that are scored on a 7-point Likert scale [24,25]. The reference period of the scale is the past two weeks. Four aspects of fatigue are measured: subjective fatigue (somatic symptoms and general feelings of fatigue), reduction in motivation, reduction in concentration, and reduction in activity. The items do not refer to the work situation but are stated in general terms. The CIS is developed for clinical populations and has often been used in patients with chronic fatigue. Beurskens et al found that the CIS was able to discriminate between fatigued and non-fatigued employees in occupational groups [26].

3. The third outcome measure is depressive complaints. Three instruments are used to measure several aspects of depressive complaints. First, self-reported depressive feelings are rated on an eleven-point scale anchored by zero for "no complaints" and ten for "much complaints. Second, the Four Dimensional Symptom Questionnaire (4DSQ) is used under the assumption that mothers may experience distress as well as somatization. The 4DSQ is a Dutch self-rating questionnaire measuring four dimensions of common psychopathology: depression (severe anhedonia and depressive thoughts), anxiety (free floating anxiety, panic, and phobic anxiety), distress (non-specific symptoms of psychopathology), and somatization (a range of common physical symptoms)[27]. The 4DSQ is developed in general practice. Reliability of the 4DSQ scales is high and has good correlation. The factor structure of the 4DSQ has been confirmed[28]. Third, the Edinburgh Postnatal Depression Scale (EPDS) is used, because of its widely use in postnatal depression research. The EPDS is a 10-item self-rating depression scale[29]. The Dutch version of EPDS is found to be a self-rating scale with good psychometric characteristics [30]. In addition to depression, the instrument also measures anxiety [31].

#### Prognostic measures

Information is gathered on a number of variables that are considered to be prognostic factors for sick leave, RTW or for the development of complaints such as pregnancy-related pelvic girdle pain, fatigue and depression. Several categories of prognostic factors are distinguished: pregnancy-related, work-related, child-related, psychosocial-related and health-related prognostic factors. For each category a number of variables is measured with questionnaires. These variables are measured at different moments in time during the follow-up period. Some variables are measured with questions that have been developed specifically for the purpose of this study, while others are measured with validated measurement instruments. Table 1 shows an overview of the variables that are measured for each category, the measurement moments, and if applicable, the name of the validated instrument. Also, data are collected on possible confounders, such as age, education, marital status and ethnicity.

**Table 1 T1:** Prognostic factors

	**T0**	**T1**	**T2**	**T3**	**T4**	**T5**
**Pregnancy-related factors:**						
Complaints and sick leave during pregnancy	x	x	x			
Previous pregnancies: birth dates, complaints and sick leave	x					
Fertility	x					
Delivery: duration, at home or in hospital, experience, complications and amount of rest after delivery			x			
Maternity and parental leave; length, satisfaction			x	x		x
Breastfeeding: length and experience at work with breastfeeding or expressing milk and facilities at work			x	x	x	x
**Work-related factors:**						
Work characteristics: function, number of working hours a week, working days, physical demands, extra work, travel time, shift work, adaptation of working hours or work tasks and work satisfaction	x			x		
Decision authority, skill discretion, psychological demands, social support of executive and colleges; Job Content Questionnaire [32,33]	x				x	
Total workload; hours a week spend on household, gardening, cycling, walking, biking, sport and odd jobs		x	x	x	x	x
Looking forward to returning to work			x	x		
Work performance; World Health Organization Health and Work Performance Questionnaire (HPQ) [34], also be measured at 18, 30, 36, 42, and 48 weeks after delivery (see outcome assessments, costs)					x	x
**Child-related factors:**						
Rang order child	x					
Birth weight child			x			
Health of child			x	x	x	x
Temperament of child; Childcare Stress Inventory [35,36]			x	x		
Childcare: childcare arrangement and changes in childcare during past year			x	x	x	x
**Psycho-Social factors:**						
Daily hassles; short version of the Everyday Problems Checklist (EPCL) [37,38]		x		x		
Social support of supervisor, colleagues, spouse, family and friends; Social Support List [39-41]		x	x		x	x
Norms about childcare and work; statements from a report of The Netherlands Interdisciplinary Demographic Institute NIDI [42]		x				x
Coping; Utrecht Coping List (UCL) [43,44]		x				
Locus of health control; Multidimensional Health Locus of Control List (MHLCL) [45].		x				
Life events		x	x	x	x	x
Difficulty of leaving child at home or day-care, when the mother is working			x	x	x	
**Health-related factors:**						
Body weight and body height	x		x	x	x	x
Smoking behaviour and alcohol intake	x					
Sleep quality		x	x	x	x	x
Co-existent chronic diseases		x				
(pregnancy-related) pelvic girdle pain (see outcome cohort study)		x	x	x	x	x
PPGP aspects: pain during rest, pain at beginning of movement, pain peak, diagnosis and treatment		x	x	x		
Fatigue (see outcome cohort study)		x	x	x	x	x
Depression (see outcome cohort study)		x	x	x	x	x
Pain catastrophizing; Pain Catastrophizing Scale (PCS) [46,47]		x				
Fear of movement; Tampa scale of Kinesiophopbia (TSK) [48]			x			

T0 = baseline, between 12 weeks and 30 weeks pregnancy, T1 = 30 weeks pregnancy, T2= 6 weeks postpartum (pp), T3 = 12 weeks pp, T4 = 24 weeks pp, T5 52 weeks pp

#### Process evaluation

One-third of the participants and supervisors in the intervention group receive a short questionnaire in order to evaluate the process of the intervention. Questions about their experience of the intervention are asked as well as which factors influenced according to them the effect of the intervention. One-third of the participants in the control group also receive a short questionnaire that asks about anticipated problems related to returning to work and whether these were discussed with their supervisor. Finally, at 12 weeks after delivery, all participants are asked if they had received any attention of their supervisor, whether their supervisor had talked about RTW and whether they were satisfied about this contact. They are also asked if they had received support of the OHSP and if they were satisfied about this support.

### Sample size

Van Beukering found that in 2002 about 30% of the women were taking sick leave after the maternity leave has ended[1]. In the Mom@Work study a decrease of 10% in sick leave at the end of the maternity leave to 20% (30–10 = 20%) is expected in the intervention group. To detect this 10% difference in sick leave, a minimum of 275 women is required per group. This difference can be detected with a power (1-β) of 80% at α= 0.05. A total of at least 550 women is needed for the entire study.

### Analysis

For the RCT, data will be analysed using statistical tests such as linear regression analysis and Cox regression analysis. The dependency of the observations will be taken into account by performing a multilevel analysis. The multilevel analysis will be performed with a four-level data structure where time, participants, supervisors and companies will be defined as levels 1, 2, 3 and 4, respectively. The analyses will be adjusted for baseline and prognostic dissimilarities, if necessary. Both an intention-to-treat analysis and a per-protocol analysis will be performed. For the cohort study, multilevel analysis will be performed with a three-level data structure where time will be defined as level 1; participants, level 2; and the companies, level 3.

The economic evaluation, which will be performed from a societal perspective, will consist of an analysis of differences in the total, direct and productivity loss costs between the intervention and control group, as well as a cost-effectiveness and cost-utility analysis of the intervention compared to common practice. In the cost-effectiveness analysis, sick leave will be the effect measure and the total costs will comprise all costs except those of productivity loss. Utilities will be based on the Euroqol questionnaire [19]. Quality Adjusted Life Years (QALY) will be calculated by multiplying the utility with the amount of time a patient spends in this particular health state. Incremental costs per QALY gained will be calculated applying both Dutch and UK tariffs. Bootstrapping methods will be used to estimate 95% confidence intervals for the incremental cost-effectiveness ratios and to derive cost-effectiveness planes and acceptability curves.

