A structural contact between supervisors and women on maternity leave, supported by early medical advice of occupational physicians during maternity leave may increase the chances of RTW after maternity leave or reduce the incidence of sick leave after maternity leave. This paper describes the design of the Mom@Work study, a randomised controlled trial (RCT) and cohort study, conducted at Body@Work, Research Centre Physical Activity, Work and Health, TNO-VUmc in Amsterdam, The Netherlands. The Mom@Work study has three aims. The first aim is to investigate the effectiveness and cost-effectiveness of an early intervention in reducing sick leave in women after maternity leave in a randomised clinical trial. Our hypothesis is that supervisors who have structural contact with their employees during maternity leave combined with occupational health care, when needed, will be more effective in reducing the number of sick leave days after maternity leave than supervisors who do not. The second aim of the study is to examine which factors contribute to RTW for women after childbirth. The third aim is to examine which factors contribute to the development of the following postpartum complaints: pregnancy-related pelvic girdle pain, depression and fatigue. The second and third aim are examined in the cohort study.

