#### Specific inclusion and exclusion criteria RCT

The inclusion criteria for the RCT were stricter than for the cohort study. Women could only enter the RCT if they met the criteria of the cohort study and the following inclusion criteria: employment for a minimum of 12 hours a week until six months after the delivery and working for the same employer before and after maternity leave.

The specific exclusion criteria for the RCT were: a delivery before thirty-four weeks; return to the same employer after maternity leave is uncertain; and definitely not returning to the same employer after maternity leave. All participants of the RCT took also part in the cohort study. Women, who were not admitted to the RCT, could enter the cohort study if they met the inclusion criteria of the cohort study. Figure 1 shows an overview of the inclusion and exclusion criteria for the RCT and cohort study.

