### Group allocation

Due to the fact that most supervisors managed a team of employees, the possibility existed that more than one employee would participate in the Mom@Work study. Thus, randomisation took place at the level of the supervisor rather than the participating woman. For each participating company, a randomisation list was computer-generated by an independent statistician. Because it was not known how many employees of each company would be participating in the study and some companies had a small number of employees, random allocation in blocks of four was chosen. Each block contained two intervention and two control group allocations in a random sequence. The details of the randomisation were printed on tickets and sealed into envelopes. The outside of the envelope was marked with the company's number and a number indicating the rang order. Supervisors were randomised when the participant was 35 weeks pregnant. When the researcher was informed in time that the participant gave birth before 34 weeks, the participant was not randomised, but still included in the cohort study.

Each week during the enrolment period, a list of supervisors who were to be randomised, was printed. The researcher allocated the supervisors of the women to the intervention group or to the control group by opening the next numbered envelope. The research assistant was responsible for sending emails and information to the supervisors who were randomised into the intervention group. The supervisors who were randomised into the control group did not receive any information and were not informed that their employee was participating in the study.

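### The cohort model drops the supervisor level used for the same women in the RCT, and no handling of trial arm is stated for factors measured after allocation

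*Protocol article*

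**What the plan says.** The Analysis section gives the RCT a "four-level data structure where time, participants, supervisors and companies will be defined as levels 1, 2, 3 and 4, respectively", to account for dependent observations. For the cohort study it specifies "a three-level data structure where time will be defined as level 1; participants, level 2; and the companies, level 3". No reason is given for leaving supervisors out.

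The two analyses share women. Under the RCT eligibility criteria: "All participants of the RCT took also part in the cohort study". The cohort also takes in others: "Women, who were not admitted to the RCT, could enter the cohort study if they met the inclusion criteria of the cohort study". Entry to the RCT is not neutral for prognosis, because a woman is excluded when "return to the same employer after maternity leave is uncertain".

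Group allocation states that "randomisation took place at the level of the supervisor rather than the participating woman", because more than one employee of the same supervisor might take part. Randomisation is at 35 weeks of pregnancy.

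The Background makes RTW a cohort question: "The second aim of the study is to examine which factors contribute to RTW for women after childbirth". On covariates, the Analysis section says "The analyses will be adjusted for baseline and prognostic dissimilarities, if necessary". That sentence sits in the RCT text, before the cohort model, and does not mention arm.

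**The concern.** Two features of the cohort analysis need attention.

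- **Clustering.** If women with the same supervisor resemble each other in RTW, a model without that level treats them as more independent than they are. The factors most exposed are those that supervisors determine. Support from the supervisor is among the prognostic factors in Table 1.
- **Trial arm.** The cohort's RTW outcome is what the intervention is meant to change, and women from both arms are pooled. Where the call also changes a factor measured afterwards, arm is a common cause of that factor and of RTW. The factor could then look prognostic partly because it marks the women who were called. The Discussion itself says that good communication with a supervisor may act much as the structured contact does.

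At stake is the reading of the second aim, and to a lesser extent the third: which factors are reported as contributing to RTW or to complaints, and with what precision.

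**Working it through.** The article gives no figure for the cohort analysis, so there is none to reproduce. It also gives no number of women per supervisor and no intraclass correlation (ICC). Those values are assumed below and shown as ranges.

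**1. Timing (Group allocation, Intervention group, Table 1).** T0 (12 to 30 weeks of pregnancy) and T1 (30 weeks) precede randomisation at 35 weeks. The call is made in the sixth week after delivery, so T2 (six weeks) may fall just before or just after it. T3 (12 weeks), T4 (24 weeks) and T5 (52 weeks) follow it. Examples of factors the call could change:
- social support of the supervisor: T1, T2, T4, T5
- support of the executive (Job Content Questionnaire): T0, T4
- looking forward to returning to work: T2, T3

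**2. Supervisor level omitted.** For a factor that is constant within supervisor, the ratio of the correct to the reported standard error is √(1 + (m − 1) × ICC), where m is the number of women per supervisor. This is an upper bound; factors that vary between women of the same supervisor are affected less.

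| m | ICC 0.01 | ICC 0.05 | ICC 0.10 | ICC 0.20 |
|---|---|---|---|---|
| 1 | 1.000 | 1.000 | 1.000 | 1.000 |
| 1.5 | 1.002 | 1.012 | 1.025 | 1.049 |
| 2 | 1.005 | 1.025 | 1.049 | 1.095 |
| 3 | 1.010 | 1.049 | 1.095 | 1.183 |

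For example, m = 2 and ICC = 0.20 give √1.20 = 1.095.

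**3. Arm omitted, factor measured before randomisation.** The planning values in Sample size are 30% sick leave in control and 20% in intervention, so the odds ratio for arm is (0.20/0.80)/(0.30/0.70) = 0.583. Take arms of equal size and a binary factor present in 30% of both arms (assumed). True odds ratios of 1.0, 1.5, 2.0 and 3.0 become 1.00, 1.49, 1.98 and 2.95 when arm is left out. The change is 2% or less. It is non-collapsibility of the odds ratio, not confounding.

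**4. Arm omitted, factor changed by the call.** Let the factor have no effect of its own (true odds ratio 1.00).
- Raised from 30% to 40%: sick leave is (0.3×0.3 + 0.4×0.2)/0.7 = 0.243 with the factor and (0.7×0.3 + 0.6×0.2)/1.3 = 0.254 without it. Odds ratio 0.94.
- Lowered from 30% to 20%: (0.3×0.3 + 0.2×0.2)/0.5 = 0.260 against (0.7×0.3 + 0.8×0.2)/1.5 = 0.247. Odds ratio 1.07.
- Much larger shifts: 30% to 60% gives 0.233 against 0.264, odds ratio 0.85; 20% against 80% gives 0.22 against 0.28, odds ratio 0.73.

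With a true odds ratio of 2.0, the two 10-point shifts give 1.87 and 2.13. Within each arm the association is the true one, so including arm removes the distortion.

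Steps 3 and 4 treat all women as randomised and use sick leave at the end of maternity leave as a stand-in for RTW. Never-randomised women would dilute the contrast between arms. They also add one that randomisation does not balance, because RCT entry depends on certainty of return.

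**The case against.** The cohort sentence describes levels only. The RCT sentence lists no allocation term either, and nobody would conclude that the RCT analysis ignores allocation. Covariate lists are commonly left to a fuller plan. This stands: a reader might infer that the cohort model omits arm, but the article is silent on the point.

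A reader might also infer that the cohort associations with RTW are confounded by arm in general. The documents do not support that. Allocation is random and follows T0 and T1, so the many factors measured then (coping, locus of control, previous pregnancies, complaints in pregnancy) are independent of arm in expectation among randomised women.

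The timetable narrows the point further. Supervisor support at T4 and T5 comes after the end of scheduled leave, and T2 roughly coincides with the call. The odds ratios of 0.85 and 0.73 need a single phone call to move reported support by 30 or 60 points, while control supervisors keep their usual contacts. Nothing in the article supports shifts of that size.

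On clustering, the supervisor is the unit of randomisation in the RCT, which makes the level essential there, whereas most cohort factors are the individual woman's own report. The article speaks only of a possibility that supervisors are shared. It would therefore go too far to say that the standard errors are wrong. For women outside the RCT the supervisor may not even be recorded.

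What remains is that the level structure is stated, not left open. It differs between two analyses of overlapping women, and no reason is given.

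**Conclusion.** The point holds in a limited form. The omission of the supervisor level is explicit and inconsistent with the RCT model for the same women. Its cost ranges from nothing, at one woman per supervisor, to a standard error that should be up to about 9.5% larger at two (18.3% at three), with an assumed ICC of 0.20 and a factor constant within supervisor. Without cluster sizes and an ICC, no more can be said than that intervals may be too narrow.

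On arm, the pooling of intervention, control and never-randomised women is stated, but its handling is not. The risk is confined to factors measured after allocation that the call could change, such as supervisor support at T4 and T5 or looking forward to work at T3. It is about 6-7% on the odds ratio for an assumed 10-point shift and grows with the shift. Factors from T0 and T1 are not confounded by arm among randomised women. The comparison of RCT with cohort-only women is a separate matter, because that membership is not random.

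**What to change.** - Use the structure of time, participant, supervisor and company in the cohort analysis too. Treat cohort-only women whose supervisor is not recorded as single clusters. Report how many women share a supervisor.
- Include a three-category fixed covariate (intervention, control, not randomised) in the RTW and complaint models.
- As a sensitivity analysis, repeat the RTW models for post-allocation factors without the intervention arm.

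The cost is a change of analysis wording and some extra model fitting. The Blinding section says that participants, supervisors and companies are coded, so RCT women need no new data collection. Intervals may become slightly wider.
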